***Statistical Analysis***

The analysis of the outcome variables will be performed on the intention–to-treat (ITT) population for the reduced dose MenC objectives and the completers population for the alternating limb objectives. A subject is included in the ITT population if they have at least one dose and at least one post-baseline assessment, and in the completers population if they receive all doses of vaccine and have all planned assessments.

An analysis of variance will be performed when the outcome variable is continuous. The model will contain the terms dose group (4 levels) and alternating limb group (2 levels). A term for centre will be included in the model. The results of a comparison between any two levels of a factor will be reported as a treatment effect with 95% confidence interval.

For the analysis of variables relating only to 0 dose control group the term relating to dose group will be omitted.

The following outcomes will be analysed (comparisons of interest are listed):

1. MenC rSBA GMT response variable assessed 28 days after the Hib-MenC 12 month booster dose
   1. Single dose MenC-CRM197 Group vs. Two dose MenC Group
   2. Single dose MenC-CRM197 Group vs. 0 dose control Group
   3. Single dose MenC-TT Group vs 0 dose control Group
   4. Two dose MenC Group vs. 0 dose control Group
   5. Single Dose MenC-CRM197 Group vs Single Dose MenC-TT Group
2. MenC rSBA GMT response variable assessed 6 days after the Hib-MenC 12 month booster dose
   1. Single dose MenC-CRM197 Group vs. Two dose MenC Group
   2. Single dose MenC-CRM197 Group vs. 0 dose control Group
   3. Single dose MenC-TT Group vs 0 dose control Group
   4. Two dose MenC Group vs. 0 dose control Group
   5. Single dose MenC-CRM197 Group vs Single dose MenC-TT Group

3. MenC rSBA GMT response variable assessed 12 months after the Hib-MenC 12 month booster dose

1. Single dose MenC-CRM197 Group vs. Two dose MenC Group
2. Single dose MenC-CRM197 Group vs. 0 dose control Group
3. Single dose MenC-TT Group vs 0 dose control Group
4. Two dose MenC Group vs. 0 dose control Group
5. Single dose MenC-CRM197 Group vs Single dose MenC-TT Group
6. MenC rSBA GMT response variable (persistence) assessed at 12 months of age
   1. Single dose MenC-CRM197 Group vs. Two dose MenC Group
   2. Single dose MenC-CRM197 Group vs. 0 dose control Group
   3. Single dose MenC-TT Group vs 0 dose control Group
   4. Two dose MenC Group vs. 0 dose control Group

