14. the *S. pneumoniae* IgG GMC response variable for each of the thirteen serotypes separately, (persistence) at 12 months of age
    1. the consistent limb group vs. the alternating limb group

1. the *S. pneumoniae* IgG GMC response variable for each of the thirteen serotypes separately at 13 months of age after the PCV-13 booster dose
   1. the consistent limb group vs. the alternating limb group
2. 12. the *S. pneumoniae* IgG GMC response variable for each of the 13 serotypes separately at 24 months of age.
   1. the consistent limb group vs. the alternating limb group

1. the anti-PRP IgG GMC response variable at 5 months of age
   1. the consistent limb group vs. the alternating limb group
2. the anti-PRP IgG GMC response variable (persistence) at 12 months of age
   1. the consistent limb group vs. the alternating limb group

1. the anti-PRP IgG GMC response variable at 13 months of age, after the Hib-MenC booster dose
   1. the consistent limb group vs. the alternating limb group
2. the anti-PRP IgG GMC response variable at 24 months of age
   1. the consistent limb group vs. the alternating limb group
3. the anti-tetanus toxoid GMC response variable at 5 months of age ,
   1. the consistent limb group vs. the alternating limb group
4. the anti-tetanus toxoid GMC response variable (persistence) at 12 months of age
   1. the consistent limb group vs. the alternating limb group

1. the anti-tetanus toxoid GMC response variable at 13 months of age
   1. the consistent limb group vs. the alternating limb group
2. the anti-tetanus toxoid GMC response variable at 24 months of age
   1. the consistent limb group vs. the alternating limb group

The binary variables will be analysed using logistic regression. The model will contain the terms dose group (4 levels), and alternating limb group (2 levels). There will also be a term for centre. The results of a comparison between two levels of a factor will be reported as an odds ratio and as a risk difference, with 95% confidence intervals.

For the analysis of variables relating only to 0 dose control group the term for dose group will be omitted.

The following binary outcomes will be analysed:

1. percentage of infants with MenC rSBA ≥ 1:8 and ≥ 1:128 assessed 6 days after the 12 month Hib-MenC booster
   1. Single dose MenC-CRM197 Group vs. Two dose MenC Group
   2. Single dose MenC-CRM197 Group vs. 0 dose control Group
   3. Single dose MenC-TT Group vs 0 dose control Group

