   4. Two dose MenC Group vs. 0 dose control Group
   5. Single dose MenC-CRM197 Group vs Single dose MenC-TT Group

1. percentage of infants with MenC rSBA ≥ 1:8 and ≥ 1:128 assessed 28 days after the 12 month Hib-MenC booster
   1. Single dose MenC-CRM197 Group vs. Two dose MenC Group
   2. Single dose MenC-CRM197 Group vs. 0 dose control Group
   3. Single dose MenC-TT Group vs 0 dose control Group
   4. Two dose MenC Group vs. 0 dose control Group
   5. Single dose MenC-CRM197 Group vs Single dose MenC-TT Group

1. percentage of infants with MenC rSBA ≥ 1:8 and ≥1:128 assessed at 12 months of age
   1. Single dose MenC-CRM197 Group vs. Two dose MenC Group
   2. Single dose MenC-CRM197 Group vs. 0 dose control Group
   3. Single dose MenC-TT Group vs 0 dose control Group
   4. Two dose MenC Group vs. 0 dose control Group
   5. Single dose MenC-CRM197 Group vs Single dose MenC-TT Group
2. percentage of infants with MenC rSBA ≥ 1:8 and ≥1:128 at 5 months of age
   1. Single dose MenC-CRM197 Group vs. Two dose MenC Group
   2. Single dose MenC-CRM197 Group vs. 0 dose control Group
   3. Single dose MenC-TT Group vs 0 dose control Group
   4. Two dose MenC Group vs. 0 dose control Group
   5. Single dose MenC-CRM197 Group vs Single dose MenC-TT Group
3. percentage of infants with MenC rSBA ≥ 1:8 and ≥1:128 at 24 months of age
   1. Single dose MenC-CRM197 Group vs. Two dose MenC Group
   2. Single dose MenC-CRM197 Group vs. 0 dose control Group
   3. Single dose MenC-TT Group vs 0 dose control Group
   4. Two dose MenC Group vs. 0 dose control Group
   5. Single dose MenC-CRM197 Group vs Single dose MenC-TT Group
4. percentage of infants with MenC rSBA GMT ≥ 1000 assessed 6 days after the 12 month Hib-MenC booster
   1. Single dose MenC-CRM197 Group vs. Two dose MenC Group
   2. Single dose MenC-CRM197 Group vs. 0 dose control Group
   3. Single dose MenC-TT Group vs 0 dose control Group
   4. Two dose MenC Group vs. 0 dose control Group
   5. Single dose MenC-CRM197 Group vs Single dose MenC-TT Group
5. percentage of infants with MenC rSBA GMT ≥ 1000 assessed 28 days after the 12 month Hib-MenC booster
   1. Single dose MenC-CRM197 Group vs. Two dose MenC Group
   2. Single dose MenC-CRM197 Group vs. 0 dose control Group
   3. Single dose MenC-TT Group vs 0 dose control Group
   4. Two dose MenC Group vs. 0 dose control Group
   5. Single dose MenC-CRM197 Group vs Single dose MenC-TT Group

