## 9.2 The Number of Participants

This is a non-inferiority trial assessing whether there is any difference in the antibody level between infants who receive no priming doses of MenC and those who receive 1 priming dose or 2 priming doses of MenC-CRM197.

The total sample size for the study is 498 participants randomised on a 10:10:7:4 basis to the 4 study groups. This will result in 160 participants in the Two Dose MenC group, 160 in the Single Dose MenC-CRM197 group, 114 in the Single Dose MenC-TT group, and 64 in 0 dose MenC (Control) group. Based on a mean (SD) log SBA of 3.47 (0.9) at 1 month after booster for 2 dose MenC12, 160 participants per group are required for the comparison between the Single Dose MenC-CRM197 and the Two dose MenC groups to detect 10% non-inferiority with a 2.5% level of significance (1-sided), 90% power and allowing for a 12.5% drop-out rate. An additional 114 participants will be required for the Single Dose MenC-TT group to allow a comparison with the Single Dose MenC-CRM197 primed group, allowing for a 12.5% drop-out rate.

No sample size calculation for the alternate limb component of the trial is included as the data generated here will be pilot data.

| Non-inferiority margi | Estimated difference | Power | Sample size required per group | Total sample size required |
| --- | --- | --- | --- | --- |
| 5% | -0.18 | 90% | 526 | 1052 |
|  |  | 80% | 393 | 786 |
| 7.5% | -0.26 | 90% | 253 | 506 |
|  |  | 80% | 190 | 380 |
| **10%** | **-0.35** | **90%** | **140*** | **280** |
|  |  | 80% | 105 | 210 |

** Requires 160 participants per group when allowing for a ‘dropout’ rate of 12.5%*

A previous study has shown the mean (SD) logSBA=2.85 (0.48) at 1 month following a 12 month dose of MenC vaccine with no prior MenC immmunisation43. Making the reasonable assumption that the SBA titres are relatively stable in the one month period after the vaccination, these statistics were used to calculate a sample size for a comparison between the one dose group and 0 dose control group at 6 days after the 12 month vaccination.

To detect a difference of 0.285 (10% of 2.85) between groups of equal size of 56 with a significance level of 0.05 (2-sided), would provide a power of 88%. Allowing for 12.5% drop outs, the initial size of 0 dose control group should be 64 infants. This therefore enables the 6 day blood test to be performed on only a subset of participants (64) in each of the other groups.

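### The odds ratio fixed for rSBA ≥1:8 at 28 days after the booster will very probably not be finite on the protocol's own planning figures; the pooled four-group ANOVA is a smaller, related mismatch

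*Protocol*

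**What the plan says.** Section 9.1 of the protocol (Statistical Analysis) fixes one method for each type of outcome.

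- Binary outcomes: "The binary variables will be analysed using logistic regression". The terms are dose group (4 levels), limb group (2 levels) and centre. Each pairwise comparison "will be reported as an odds ratio and as a risk difference, with 95% confidence intervals". The listed outcomes include "percentage of infants with MenC rSBA ≥ 1:8 and ≥ 1:128 assessed 28 days after the 12 month Hib-MenC booster" and "percentage of infants with MenC rSBA ≥ 1:8 and ≥ 1:128 assessed 6 days after the 12 month Hib-MenC booster", each with five comparisons between dose groups.
- Continuous outcomes: "An analysis of variance will be performed when the outcome variable is continuous". One model covers all four dose groups, with limb group and centre. No variance structure is mentioned.

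Section 9.2 gives the distributions used for planning. For the two-dose group: "Based on a mean (SD) log SBA of 3.47 (0.9) at 1 month after booster for 2 dose MenC". For unprimed children: "mean (SD) logSBA=2.85 (0.48) at 1 month following a 12 month dose of MenC vaccine with no prior MenC". The Assumptions list in the same section adds log10 rSBA of 3.784 (SD 0.421) at 30 days and 3.673 (SD 0.252) at 6 days after a 12-month booster. The protocol text gives no rule for groups at 0% or 100%, or for unequal variances.

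**The concern.** The threshold 1:8 is 0.903 on the log10 scale, two or more units below most of these planning means. A logistic model estimates a finite odds ratio between two groups only if each group has at least one child on each side of the threshold. If a group has no child below 1:8, its coefficient runs off to infinity. Software then returns an arbitrary large number with a meaningless standard error. The protocol would be committing itself to a measure that its own figures say it should not expect to obtain. The replacement would be chosen after the data are in, in an open-label trial.

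A milder form of the same mismatch affects the continuous outcomes. An ordinary ANOVA uses one pooled error variance, while the planning SDs at about one month are 0.9 and 0.48. That bears on interval widths for all dose-group contrasts, including the primary one.

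**Working it through.** **Reproducing the plan's figures.** With margin 0.35, SD 0.9, one-sided 2.5% and 90% power, n = 2 × 0.9² × (1.960 + 1.282)² / 0.35² ≈ 139 per group (142 with a margin of 0.347). The protocol states 140, and 140/0.875 = 160. For day 6, 56 per group, difference 0.285 and SD 0.48 give power 0.881, against the stated 88%. Evaluable numbers after 12.5% drop-out are about 140, 140, 100 and 56.

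**Chance that a child is below 1:8.** Assuming normal log10 titres, q = Φ((0.903 − mean)/SD).

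| Planning figure | q | Expected below 1:8 | P(none below) = (1 − q)^n |
|---|---|---|---|
| Two-dose, day 28: 3.47 / 0.9 | 0.00217 | 0.30 of 140 | 0.738 |
| Single-dose mean at the margin: 3.12 / 0.9 | 0.00688 | 0.96 of 140 | 0.380 |
| MenC-TT, same values assumed: 3.47 / 0.9 | 0.00217 | 0.22 of 100 | 0.805 |
| Unprimed, day 28: 2.85 / 0.48 | 0.000025 | 0.001 of 56 | 0.9986 |
| Assumptions list, 30 days: 3.784 / 0.421 | 4 × 10⁻¹² | 0 of 140 | 1.000 |
| Assumptions list, 6 days: 3.673 / 0.252 | 2 × 10⁻²⁸ | 0 of 56 | 1.000 |

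**Chance of no finite odds ratio.** This is 1 − (1 − P₀ of one group) × (1 − P₀ of the other), where P₀ is the last column.

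- MenC-CRM197 vs two-dose, equal means: 1 − 0.262 × 0.262 = 0.93
- MenC-CRM197 vs two-dose, single-dose mean at the margin: 1 − 0.262 × 0.620 = 0.84
- MenC-CRM197 vs MenC-TT: 1 − 0.262 × 0.195 = 0.95
- MenC-CRM197 vs Control: 1 − 0.262 × 0.0014 = over 0.999
- On the Assumptions list figures: about 1 between primed groups, at 30 days and at 6 days

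The chance that no child in the whole trial is below 1:8 at day 28 is 0.738² × 0.805 × 0.9986 = 0.44.

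**Sensitivity.** The planning SDs do not allow for a separate set of non-responders. With an assumed failure rate in both groups of 140, the chance of no finite odds ratio is 75% at 0.5%, 43% at 1% and 11% at 2%. For 140 against 56 it is 88%, 67% and 36%.

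**Risk difference when both groups are at 100%.** The Wald standard error is √(1 × 0/140 + 1 × 0/56) = 0, so that interval collapses to a point. A Newcombe interval does not. The Wilson lower limits are 140/(140 + 3.84) = 0.973 and 56/(56 + 3.84) = 0.936, which gives −2.7 to +6.4 percentage points.

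**ANOVA.** Pooled variance = Σ(n − 1)SD² / (N − 4). For SDs 0.9/0.9/0.9/0.48 (0.9 assumed for MenC-TT) this is 318.0/432 = 0.736, so the pooled SD is 0.858. For the primary contrast the ratio of pooled to separate-variance width is 0.858/0.9 = 0.953. The one-sided error is 1 − Φ(1.96 × 0.953) = 3.1%. Against Control, the ratio is 0.858 × √(1/140 + 1/56) = 0.136 over √(0.81/140 + 0.2304/56) = 0.0995, which is 1.36. The other rows follow the same formulas, with 56 per group at day 6.

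| SDs, primed / Control | Primed vs primed: ratio (coverage) | MenC-CRM197 vs Control: ratio (coverage) |
|---|---|---|
| Day 28: 0.9 / 0.48 | 0.95 (93.8%) | 1.36 (about 99%) |
| Day 28: 0.421 / 0.48 | 1.02 (95.4%) | 0.925 (93.0%) |
| Day 6: 0.252 / 0.48 | 1.29 (98.8%) | 0.85 (90.3%) |

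**The case against.** The strongest reply is that zero-cell rules, interval methods and robust standard errors belong in a SAP, which was not available for this check. That is fair for missing detail. It does not cover a model and an effect measure that the protocol positively fixes and that its own figures say will not deliver.

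A second reply is that the probabilities lean on normal tails; the Control figure lies four SDs out. This stands. The result is a probability, and a non-response rate of about 2% would usually give a finite odds ratio.

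A reader might also infer several stronger things that the protocol does not support:

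- *That the seroprotection comparisons cannot be produced at all.* The protocol also asks for a risk difference, which can be estimated from proportions at 100%.
- *That the problem covers every post-booster visit.* There is no planning figure for 24 months of age.
- *That it covers Controls at day 6.* Section 9.2 carries the one-month unprimed figures over to day 6, whereas the Rationale looks for a day-6 rise in primed but not unprimed infants. The Control distribution is unsettled.
- *That Controls are at the floor before the booster.* This is plausible, but no figure is given.
- *That ≥1:128 fails in the same way.* At day 28 with 3.47/0.9 and 2.85/0.48, about 9.1 of 140 and 3.4 of 56 fall below, which is usually estimable. Only SD 0.421 makes it inestimable (0.005 of 140).
- *That the ANOVA fails, or is always too narrow between primed groups and too wide against Control.* Point estimates stay valid, and the direction reverses on the Assumptions list SDs. The 0.9 and 0.48 also come from different sources. Section 9.3 attributes 3.47 to a study that, according to the Rationale, used a plain polysaccharide challenge at 12 months rather than Hib-MenC.

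**Conclusion.** The point holds for rSBA ≥1:8. At 28 days after the booster, the specified odds ratio has an 84% to over 99.9% chance of not being finite, depending on the comparison, if log titres are normal with the planning means and SDs. At day 6 the same holds between primed groups on the Assumptions list figures. The risk difference survives, but a Wald interval taken from the separated model would degenerate. These are secondary endpoints, so the primary conclusion does not depend on this part.

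The ANOVA point is secondary and can go either way. For the primary contrast the width is off by about 2% to 5%. At worst the one-sided error is 3.1% instead of 2.5%, which requires SD 0.9 in all primed groups, including MenC-TT. The larger effects are in contrasts with Control, from 36% too wide at day 28 to about 90% coverage at day 6. The day-6 figure rests on the protocol's assumption that the one-month unprimed SD of 0.48 also applies at day 6.

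**What to change.** For binary outcomes, make the risk difference the main measure, with a Miettinen-Nurminen score interval or a Newcombe interval. Keep the odds ratio, but state that it will be Firth-penalised or exact whenever a group is at 0% or 100%.

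For continuous outcomes, keep dose group, limb group and centre in the model, but allow group-specific residual variances or use HC3 standard errors, including for the primary contrast.

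The cost is wording in section 9.1 and the SAP, plus standard software options. No change to design or sample size is needed, and the only statistical price is a few degrees of freedom. If the SAP already contains such rules, section 9.1 should be aligned with it.

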**C) Analysis of safety**

The data summaries will report the total number and percentage of infants experiencing each type of adverse event, and the total number and percentage of infants experiencing at least one adverse event of any type, for each dose group, and the total number of infants in each dose group, for local and general adverse events during the 4-day follow-up period after each MenC (including Hib-MenC), DTaP-IPV-Hib and PCV13 vaccination. The classification of severity of local adverse events and fever will follow the Brighton collaboration guidelines 35 - 38.

Where the adverse event is further classified with a grade (1, 2, 3) related to severity, the summary reports will include the numbers in each class.

**Statistical analysis**

The binary variables will be analysed using logistic regression. The model will contain the terms dose group (4 levels) and alternating limb group (2 levels). A term for centre will be included in the model. The results of a comparison between two levels of a factor will be reported as an odds ratio and as a risk difference, with 95% confidence intervals.

The following variables will be analysed:

**Local adverse events**

1. percentage of infants with each type of adverse event, and at least one local adverse event after each dose of MenC vaccine (at 3 and 4 months)
   1. Single dose MenC-CRM197 Group vs. Two dose MenC Group
   2. Single Dose MenC-CRM197 Group vs Single Dose MenC-TT Group
2. percentage of infants with each type of adverse event, and at least one local adverse event after each dose of DTaP-IPV-Hib (at 2, 3 and 4 months) and PCV13 (at 2 and 4 months)
   1. the consistent limb group vs. the alternating limb group
3. percentage of infants with each type of adverse event, and at least one local adverse event after the 12 month booster Hib-MenC and PCV13 vaccination
   1. Two dose MenC Group vs. 0 dose control Group
   2. Single dose MenC-CRM197 Group vs. 0 dose control Group
   3. Single dose MenC-CRM197 Group vs. Two dose MenC Group
   4. Single dose MenC-TT Group vs 0 dose control Group
   5. Single dose MenC-CRM197 Group vs Single dose MenC-TT Group
   6. the consistent limb group vs. the alternating limb group

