***Single dose MenC-CRM197 Group n=160**

MenC-CRM197 at 3 months

Visit 5

Visit 6**

Visit 7

Hib-MenC boost + PCV13 at 12 months

VP

VP

VP

VP

*Control group n=64

Visit 2

Visit 3

MMR

Visit 8

VP

*Single dose MenC-TT Group n=114 MenC-TT at 3 months

*Participants would be randomised to receive MenC-CRM197 at 3 and 4 months (Two Dose MenC Group), or a single dose at 3 months (Single Dose MenC-CRM197 Group) or a single dose of MenC-TT at 3 months (Single dose MenC-TT Group) or no priming doses (Control Group). All participants will receive the DTaP-IPV-Hib vaccine at 2, 3 and 4 months and the PCV13 at 2 and 4 months according to the UK immunisation schedule. All participants would be boosted with the Hib-MenC vaccine and the booster dose of PCV13 at 12 months and will receive the MMR vaccine at 13 months.

Venepuncture (VP), taking 5 ml of blood, will be performed at 5 months (Visit 4), and taking 7.5ml of blood will be performed at 12 months (Visit 5), 12 months+6 days (Visit 6), at 13 months (Visit 7) and at 24 months (Visit 8). Two attempts may be made to obtain a blood sample at each visit, if the parent gives verbal consent at the time of the procedure for a second attempt. If no blood is obtained, a second visit may be made if the parent agrees to this.

** Visit 6 will be performed on all participants in the control group and a subset of 64 participants in the Two Dose MenC, Single Dose MenC-CRM197 and Single Dose MenC-TT groups (as determined by randomisation at enrolment, see section 6.4.4)

In addition, participants will be randomised at enrolment to receive PCV13 and DTaP-IPV-Hib in either consistent limbs (subgroup a) or alternating limbs (subgroup b) as follows

| **Subgroup a**  (Consistent limbs) | **Subgroup b**  (Alternating limbs) |
| --- | --- |
| DTaP-IPV-Hib in right leg at 2, 3 and 4 months  PCV13 in right leg at 2, 4and 12 months | DTaP-IPV-Hib in left leg at 2 months and in right leg at 3 and 4 months*  PCV13 in left leg at 2 months, right leg at 4 months and left arm at 12 months |

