2. Serotype specific pneumococcal B cell phenotype in a subset of participants at 5, 12, 13 and 24 months of age in children receiving PCV13 in a consistent limb (sub groups ‘a’) vs those receiving this in alternating limbs (subgroups ‘b’).

3. Anti-PRP IgG GMCs or percentage of infants with serum concentration of anti-PRP IgG ≥ 0.15 g/mL and ≥1.0 g/ml at 5, 12, 13 and 24 months of age in children receiving DTaP-IPV-Hib in a consistent limb (sub groups ‘a’) vs those receiving this in alternating limbs (subgroups ‘b’).

4. Anti-tetanus toxoid GMCs or percentage of participants with anti-tetanus toxoid >0.1IU/ml at 5, 12, 13 and 24 months of age in participants in receiving DTaP-IPV-Hib in a consistent limb (sub groups ‘a’) vs those receiving this in alternating limbs (subgroups ‘b’).

*Reactogenicity*

The following comparisons would be performed to assess differences between:

Local adverse events

1. The percentage of infants with each type of adverse event, and at least one adverse event for local adverse events after one dose of MenC-CRM197 at 3 months (Single Dose MenC-CRM197 Group) vs the second dose of MenC-CRM197 at 4 months (Two Dose MenC Group).
2. The percentage of infants with each type of adverse event, and at least one adverse event for local adverse events after one dose of MenC-CRM197 at 3 months (Single Dose MenC-CRM197 Group) vs one dose of MenC-TT at 3 months (Single Dose MenC-TT Group).
3. The percentage of infants with each type of adverse event, and at least one adverse event for local adverse events after each dose of DTaP-IPV-Hib (at 2, 3 and 4 months) and PCV13 (at 2 and 4 months) in the consistent limb group (sub groups ‘a’) vs. the alternating limb group (subgroups ‘b’).
4. The percentage of infants with each type of adverse event, and at least one adverse event for local adverse events after the 12 month booster MenC and PCV13 vaccination in the
   1. Two Dose MenC Group vs 0 Dose Control Group
   2. Single Dose MenC-CRM197 Group vs. 0 Dose Control Group
   3. Single Dose MenC-TT Group vs. 0 Dose Control Group
   4. Single Dose MenC-CRM197 Group vs. Two Dose MenC Group
   5. Single Dose MenC-CRM197 Group vs Single Dose MenC-TT Group
   6. the consistent limb group vs. the alternating limb group

Systemic adverse events

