# APPendix a: study flow CharT

| **Details of vaccine administration for each treatment group** | | | **Visit 1** | **Visit 2** | **Visit 3** | **Visit 4** | **Visit 5** | **Visit 6*** | **Visit 7** | **Visit 8** |
| --- | --- | --- | --- | --- | --- | --- | --- | --- | --- | --- |
|  |  |  | **Blood** | **Blood** | **Blood** | **Blood** | **Blood** |
| **Two Dose MenC Group**  **(2 doses MenC-CRM197)**  **Group 2** | **a** | Right leg | DTaP-IPV-Hib  PCV13 | DTaP-IPV-Hib | DTaP-IPV-Hib  PCV13 |  | PCV13 |  | MMR |  |
| Left leg |  | *MenC****-CRM197*** | *MenC****-CRM197*** |  | Hib-MenC |  |  |
| **b** | Right leg |  | DTaP-IPV-Hib | DTaP-IPV-Hib  PCV13 |  |  |  | MMR |  |
| Left leg/ arm | DTaP-IPV-Hib  PCV13 | *MenC***-*CRM197*** | *MenC****-CRM197*** |  | Hib-MenC (leg), PCV13 (arm) |  |  |
| **Single Dose MenC-CRM197 Group**  **(1 dose MenC-CRM197)**  **Group 1** | **a** | Right leg | DTaP-IPV-Hib  PCV13 | DTaP-IPV-Hib | DTaP-IPV-Hib  PCV13 |  | PCV13 |  | MMR |  |
| Left leg/ arm |  | *MenC***-*CRM197*** |  |  | Hib-MenC |  |  |
| **b** | Right leg |  | DTaP-IPV-Hib | DTaP-IPV-Hib  PCV13 |  |  |  | MMR |  |
| Left leg/ arm | DTaP-IPV-Hib  PCV13 | *MenC****-CRM197*** |  |  | Hib-MenC (leg) PCV13 (arm) |  |  |
| **Control Group**  **(0 dose MenC priming)**  **Group 3** | **a** | Right leg | DTaP-IPV-Hib  PCV13 | DTaP-IPV-Hib | DTaP-IPV-Hib  PCV13 |  | PCV13 |  | MMR |  |
| Left leg/ arm |  |  |  |  | Hib-MenC |  |  |
| **b** | Right leg |  | DTaP-IPV-Hib | DTaP-IPV-Hib  PCV13 |  |  |  | MMR |  |
| Left leg/ arm | DTaP-IPV-Hib  PCV13 |  |  |  | Hib-MenC (leg) PCV13 (arm) |  |  |
| **Single Dose MenC-TT Group**  **(1 dose MenC-TT)**  **Group 4** | **a** | Right leg | DTaP-IPV-Hib  PCV13 | DTaP-IPV-Hib | DTaP-IPV-Hib  PCV13 |  | PCV13 |  | MMR |  |
| Left leg/ arm |  | *MenC-TT* |  |  | Hib-MenC |  |  |
| **b** | Right leg |  | DTaP-IPV-Hib | DTaP-IPV-Hib  PCV13 |  |  |  | MMR |  |
| Left leg/ arm | DTaP-IPV-Hib  PCV13 | *MenC-TT* |  |  | Hib-MenC (leg) PCV13 (arm) |  |  |

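### Local reactions to MenC, Single Dose vs Two Dose: read literally, Section 9.1 compares identical treatment at 3 months and has no comparator at 4 months, while Section 6.2 defines a different contrast

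*Protocol*

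**What the plan says.** Protocol Section 9.1 C, Local adverse events, item 1 analyses the percentage of infants with each type of event and with "at least one local adverse event after each dose of MenC vaccine (at 3 and 4 months"). Two contrasts are listed under it: "Single dose MenC-CRM197 Group vs. Two dose MenC Group", and Single Dose MenC-CRM197 against Single Dose MenC-TT. The method is logistic regression: "The model will contain the terms dose group (4 levels) and alternating limb group (2 levels"), with a further term for centre. Results are to be given as an odds ratio and a risk difference with 95% confidence intervals.

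Section 6.2, Reactogenicity, Local adverse events, item 1 words the first contrast as "local adverse events after one dose of MenC-CRM197 at 3 months (Single Dose MenC-CRM197 Group) vs the second dose of MenC-CRM197 at 4 months" in the Two Dose group. Item 2 there places MenC-CRM197 versus MenC-TT at 3 months only.

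On what is injected, Section 6.1 says: "Participants would be randomised to receive MenC-CRM197 at 3 and 4 months (Two Dose MenC Group), or a single dose at 3 months". It also says: "All participants will receive the DTaP-IPV-Hib vaccine at 2, 3 and 4 months and the PCV13 at 2 and 4 months". Appendix A labels the Single Dose group "1 dose MenC-CRM197" and leaves its left-limb cell empty at Visit 3 in both limb subgroups.

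**The concern.** The analysis section names a contrast, two time points and a model, so this is not a detail left to a later analysis plan. Set against the vaccination schedule, the named contrast asks nothing about the vaccine at one time point and has nothing to compare at the other. The endpoint section gives a different contrast for the same outcome. Two analysts, each following one section faithfully, would report different results under one endpoint. Assessing reactions after each dose is a stated objective (Section 5.2, objective 8), so it should be clear which comparison answers it.

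**Working it through.** **Step 1. Injections by arm and visit** (Section 6.1 and Appendix A; the same in both limb subgroups at these two visits).

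| Arm (planned n) | 3 months, left leg | 3 months, right leg | 4 months, left leg | 4 months, right leg |
|---|---|---|---|---|
| Two Dose, Group 2 (160) | MenC-CRM197 | DTaP-IPV-Hib | MenC-CRM197 | DTaP-IPV-Hib, PCV13 |
| Single Dose CRM197, Group 1 (160) | MenC-CRM197 | DTaP-IPV-Hib | none | DTaP-IPV-Hib, PCV13 |
| Single Dose TT, Group 4 (114) | MenC-TT | DTaP-IPV-Hib | none | DTaP-IPV-Hib, PCV13 |
| Control, Group 3 (64) | none | DTaP-IPV-Hib | none | DTaP-IPV-Hib, PCV13 |

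**Step 2. Section 9.1 contrast at 3 months.** Groups 1 and 2 have had the same vaccines up to this visit, so the true vaccine risk difference is 0. With 140 per arm (160 less the planned 12.5% dropout), the 95% half-width is 1.96 × √(2p(1−p)/140). The protocol gives no reaction rate; for assumed p = 10%, 30% and 50% the half-width is 7.0, 10.7 and 11.7 percentage points. A nominally significant result would be chance or, in an open-label trial, reporting.

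**Step 3. Section 9.1 contrast at 4 months.** Group 1 has no MenC site. There are two ways to handle its infants:
- Left out of the denominator: Group 2 stands alone and there is no contrast.
- Coded as no event: Group 1 has 0 events by construction. The odds ratio of Group 1 to Group 2 is then 0, its logarithm has no finite estimate, and the risk difference is p₂ − 0 = p₂, which is Group 2's own rate. A trial fit with 0 of 140 against an assumed 30% did not converge. The separation is quasi-complete, because Group 2 has both events and non-events.

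Neither route gives a meaningful between-group comparison. For MenC-CRM197 versus MenC-TT at 4 months, both arms are without a MenC injection. Control has none at either age, so the four-level dose-group term includes a level with no MenC site.

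**Step 4. Section 6.2 contrast.** Group 1 at 3 months against Group 2 at 4 months changes dose number, age and visit together. Suppose there is no effect of dose number, only a visit-related shift of 5 to 10 points either way (assumed), from base rates of 10%, 30% or 50%. With 140 per arm, the chance of a nominally significant difference is Φ[(|p₄−p₃| − 1.96√(2p̄(1−p̄)/140)) / √((p₃(1−p₃)+p₄(1−p₄))/140)]. It runs from 13% (50% to 55%) to 65% (10% to 20%). The odds ratio, 4 months to 3 months, runs from (0.05/0.95)/(0.10/0.90) = 0.47 to (0.20/0.80)/(0.10/0.90) = 2.25.

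**Step 5. Using both MenC-CRM197 arms at 3 months against MenC-TT.**
- Standard error ratio: √(1/320 + 1/114) / √(1/160 + 1/114) = 0.1091/0.1226 = 0.890.
- Half-width at an assumed 30%: 1.96 × √0.21 × 0.1226 = 11.0 points, against 1.96 × √0.21 × 0.1091 = 9.8 points.
- Equal dropout across arms leaves the ratio unchanged.

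**Step 6. Pairing dose 2 with dose 1 within Group 2.** Relative to an unpaired comparison of the same size with similar rates, the standard error is multiplied by √(1−ρ): 0.89, 0.84 and 0.71 for an assumed within-infant correlation of 0.2, 0.3 and 0.5.

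**The case against.** The two sections list the same two contrasts in the same order, so the ages in Section 9.1 could merely name when the doses in Section 6.2 are given. On that reading there is no null comparison and no uninjected comparator. This reading is possible, but a contrast of two groups after each dose at two ages more naturally means one comparison at each age, and nothing in Section 9.1 points back to Section 6.2. A cumulative reading (any MenC-site reaction over the whole course) would also be coherent, but neither section says it.

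A reader might infer that the planned model must fail. The protocol does not support that: the odds ratio diverges only if uninjected infants are coded as no event, which is nowhere stated, and the planned risk difference stays finite even then. The size of a non-converged coefficient says nothing about the trial.

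A reader might also infer that PCV13 seriously confounds the Section 6.2 contrast. At 4 months PCV13 goes in the right leg in both limb subgroups and MenC in the left, so its influence on the MenC site is indirect. Age and visit remain tied to dose number, but that holds for any comparison of dose 1 with dose 2 under this schedule, including a paired one; pairing gains precision only.

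Finally, MenC-CRM197 versus MenC-TT is already answerable at 3 months from 160 against 114 randomised infants, as Section 6.2 has it. Pooling is an efficiency gain and not the correction of an error. All of these limits stand. They leave the conflict between the sections and the unsupported literal contrast in place.

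**Conclusion.** The point holds in a limited form. Item 1 of the local adverse events list in Section 9.1 C, as worded, gives a comparison that is null by design at 3 months and none that is meaningful at 4 months, and it disagrees with Section 6.2. The Section 6.2 contrast is sound as a description of randomised arms but cannot isolate the effect of a second dose.

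The consequence is modest. This is a secondary safety analysis of licensed vaccines, no sample size rests on it, and the primary non-inferiority test is untouched. The finding on which injections are compared follows from the schedule alone. The sizes rest on assumed reaction rates of 10% to 50%, assumed visit shifts of 5 to 10 points and assumed within-infant correlations of 0.2 to 0.5, none of which the protocol gives.

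**What to change.** Reword item 1 identically in Sections 6.2 and 9.1 C, naming the injection, the visit and the arms for each contrast:

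- **3 months:** first-dose MenC-CRM197 (Groups 1 and 2, identically treated to that point) against MenC-TT (Group 4), with limb subgroup and centre in the model and Control omitted.
- **Dose 2 against dose 1 of MenC-CRM197:** report as descriptive and confounded with age and visit, preferably paired within Group 2 (McNemar or conditional logistic regression).
- **4 months:** the Group 2 MenC-site reaction rate with a 95% confidence interval, and no between-group odds ratio. Section 9.1 C already tabulates the count and percentage, so only the interval is new.

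The systemic-event comparison of Single Dose with Two Dose already in Section 9.1 C can stay: at 4 months it is the randomised comparison of a second dose with none.

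The cost is wording only, on the same diary data. Pooling Groups 1 and 2 departs from the pairwise layout used elsewhere. If the sponsor prefers to keep that layout, Group 1 against Group 4 at 3 months remains valid with a wider interval.
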